**DATA ANALYSIS**

Qualitative analysis will be characterized by seeking the meanings in the subjects' speech, linked to the context. After transcribing the interviews, exhaustive readings will be carried out until the entire text is exhausted, separation of the themes worked and adequacy to the objectives of the study (OLIVEIRA, 2008).

The technique basically consists of analyzing the verbal material collected in surveys that have testimonies as their raw material, extracting from each of these testimonies. Data analysis was performed using the collective subject discourse (CSD), a technique developed by Lefèvre and Lefèvre to organize the material resulting from fieldwork, usually from speeches from interviews. The result is a synthesis-discourse, the result of fragments of individual discourses gathered by similarity of meaning. The individual speech reveals the collective speech (LEFÈVRE AND LEFÈVRE, 2006), it is the junction of individual speeches, respecting the senses and the level of sharing.

Methodological figures were used to construct the speeches: key expressions (E-Ch); central ideas (Ucs); the collective subject discourse (CSD) itself:

• The E-Ch are selected excerpts from the verbal material of each statement, which best describe the content;

• The CIs describe the meanings, or linguistic expression that reveals and describes, in a synthetic and precise way, the meaning present in the statements, using the interviewee's words, not constituting interpretation;

• The anchoring process is the manifestation of a theory, ideology or belief that the authors of the discourse profess and believe that it brings the basic idea that sustains the discourse (LEFÈVRE AND LEFÈVRE, 2005).

If contradictory statements appear regarding the same issue, the CSDs are prepared for the concordant and discordant statements; As the CSDs emerge and the system of interpretation of reality is built and relationships are established in the social context, behaviors and practices become evident, being enriched with social representations that can contribute to the understanding of health care (DUARTE, MAMEDE , ANDRADE, 2009).

The Collective Subjects' Discourses are the gathering of the E-CH present in the testimonies, which have CIs with a similar or complementary meaning, to give them the form of chained sentences. It is important to point out that the CI is not an interpretation, but a description of the meaning of a statement or a set of statements. The technique for building the DSC involves selecting, from each individual answer to a question, the E-CHs, which are the most significant parts of these answers. These E-CH correspond to ICs, which are the synthesis of the discursive content manifested in the E-CH. With the material of the E-CHs of similar CIs, synthesis discourses, or CSDs, are constructed in the first person singular, with a collectivity appearing as if it were an individual discourse. (LEFÈVRE; LEFÈVRE, 2005b).

The CSD represents the thinking of a collectivity, through a series of testimonies that culminate in synthesis discourses, which bring together responses from different individuals, with discursive content of similar meaning, which begins to express or represent social speech or collective thinking. in the first person singular (LEFÈVRE; LEFÈVRE, 2005b).

According to Lefèvre and Lefèvre (2005b), the “I” of the CSD is an attempt to rescue the “social or collective self”; more precisely, it is a resource created to bring out the social unconscious that speaks in the individual. Therefore, the CSD is a discourse to signal what society imposes on the individual through the unconscious internalization of their discourses, which is why it needs to be stated in the first person singular. The speeches reveal what the community thinks, how it thinks, and how this thought is distributed in the social space (LEFÈVRE; LEFÈVRE and MARQUES, 2009).

Subjects will be identified with the capital "C" consonant, followed by the Arabic number increasing from 1. Example: C1; C2; C3; C4. Duarte, MAMEDE & ANDRADE (2002) propose that the complete transcripts of the recorded testimonies be attached to the research, so that they can contribute to the reliability and legitimacy of the results. Even so, it was decided not to put this material in an appendix, as it was considered that reading the individual speeches in full could compromise the confidentiality commitment assumed with the interviewees.

# SCHEDULE

The research project will be carried out according to the following schedule:

| Stages | Duration |
| --- | --- |
| Bibliographic Review | May/2018 to February/2019 |
| Submission of the research project to CEP- CCS-UFES | April/2018 |
| Submission of the research project to the local ethics committees or municipal health departments (Brasília, Curitiba, Florianópolis, Ribeirão Preto and Vitória) | May/2018 |
| Data collection from the pragmatic trial (1st stage): Period of insertion of participants | June/2018 to March/2019 |
| Face-to-face meeting in Brasilia with all coordinators | June/2018 |
| Conducting the Cross-sectional Study | June/2018 |
| Analysis of data from the Cross-sectional Study | August/2018 |
| Delivery of the Transversal final product of the study | October/2018 |
| Conducting the qualitative study | September/2018 |
| Analysis of qualitative study data | October/2018 to December/2018 |
| Face-to-face meeting in Brasilia with all coordinators | December/2018 |
| Delivery of the qualitative final product of the study | March/2019 |
| Closing of follow-up of patients included in the Pragmatic Trial | November / 2019 |
| Analysis of data from the Pragmatic Test | December/2022 |
| Delivery of the final product of the pragmatic test | December/2022 |
| Delivery of the Final Project Report | December/2022 |

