# INTRODUCTION

The World Health Organization (WHO) defines latent Mycobacterium tuberculosis infection (LTBI) as a state of persistent immune response to stimulation by Mycobacterium tuberculosis antigens without evidence of clinical manifestations of active tuberculosis (TB). It is estimated that a quarter of the world population is infected by this bacterium. Despite the absence of symptoms, there is a risk of these patients developing active TB, especially in the first two years after the primary infection worsened in the case of immunosuppression. Activation occurs in 5-10% of cases (LEITE-JÚNIOR, 2017).

Thus, the evaluation of contacts of TB cases is of relevant importance for the screening of LTBI, which requires proper diagnosis and treatment, with the aim of preventing the development of active TB in the future, also interrupting the disease transmission cycle. In Brazil, the National Tuberculosis Control Program/Ministry of Health (PNCT) considers any person who lives in the same environment as the index case as contact at the time of diagnosis of TB. Contacts under the age of five, people with HIV and people with high-risk conditions should be considered a priority in the process of evaluating contacts and treating LTBI (BRASIL, 2017).

The drug Isoniazid is used worldwide for the treatment of LTBI and reduces the risk of illness by 60 to 90%, depending on adherence and duration of treatment (WHO, 2015). As recommended by the Health Surveillance Guide (2017), the current regimen indicated and available for the treatment of LTBI is with the presentation of Isoniazid 100mg in a dosage of 5 to 10 mg/kg/day (maximum dose of 300mg/day) in 270 doses that should be taken from 9 to 12 months (BRASIL, 2017). However, from 2018, Isoniazid 300mg will also be made available to the health network, which should be incorporated by the services. In other words, there will be two presentations of Isoniazid (100mg and 300mg) in the units studied to be used in the treatment of LTBI. Studies carried out by FIOCRUZ indicate that the two formulations have bioequivalence (Daher et al, 2015).

The two presentations of Isoniazid (100mg and 300mg) will be available to be used as needed depending on the weight range of adults and children. Since overdose of Isoniazid can lead to severe drug hepatitis and death, correct use is imperative to ensure that people undergoing treatment for LTBI receive the correct dose of Isoniazid.

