# OBJECTIVE

• To analyze the occurrence of serious or unexpected adverse reactions resulting from the use of Isoniazid 300mg by the patient for the treatment of latent tuberculosis infection.

• To analyze the patient's use of Isoniazid 300mg for the treatment of latent tuberculosis infection.

• To analyze the information strategies made available to health services on the new presentation of Isoniazid 300mg for the treatment of latent tuberculosis infection.

• To analyze compliance in the prescription of Isoniazid 300mg for the treatment of latent tuberculosis infection through the Knowledge, Attitudes and Practices (CAP) strategy.

•To analyze compliance in the dispensing of Isoniazid 300mg for the treatment of latent tuberculosis infection through the Knowledge, Attitudes and Practices (CAP) strategy.

• To determine the plasma levels of patients undergoing treatment with Isoniazid 100 and 300mg

• To analyze the social representations of health professionals from the basic unit on the use of Isoniazid 300mg for the treatment of latent tuberculosis infection.

• To know the meanings of health professionals at the basic unit about the use of Isoniazid 300mg for the treatment of latent tuberculosis infection.

• To identify the role of health professionals from the basic unit in relation to patients using Isoniazid 300mg for the treatment of latent tuberculosis infection.

• To interpret how health professionals at the basic unit relate their conceptions to the prescription of Isoniazid 300mg for the treatment of latent tuberculosis infection.

• To develop and analyze the use of a computerized system for mobile devices that helps health professionals in the diagnosis and treatment process, as well as to assist in the prevention and care of people with latent Tuberculosis, evaluating its use in these health services to integrate follow-up actions as well as evaluating the degree of solvability of these actions from the system.

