# METHODS

STUDY STEPS

First step

Research sites and Study design

This step will be carried out in Brasília, Curitiba, Santa Catarina, Ribeirão Preto, Espírito Santo in the form of a pragmatic, open-label, randomized clinical trial in health units that provide care to patients with Tuberculosis and whether or not they have a Tuberculosis Control Program (PCT acronym in Portuguese). ). The health facilities that prescribe LTBI treatment will be chosen. From June 2018 to March 2019, people over 18 years of age with indication for LTBI treatment will be invited to participate in this study.

After signing the informed consent term, the contacts will be randomized to receive Isoniazid 100mg or 300mg and will be followed up until the end of treatment.

The primary outcome will be the success rate of LTBI treatment in the new 300mg formulation represented by the proportion of subjects with 270 doses of isoniazid between 9 to 12 months.

Secondary outcomes will be evaluated by comparing adverse effects in the two groups (Isoniazid 100mg or 300mg).

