**Data analysis:**

The variables will be summarized using measures of frequency, and of central tendency and dispersion, being those that concern knowledge, attitudes and practices in the face of LTBI care. Categorical covariates will be tested using Pearson's chi-square test (or Fischer's Exact test) and continuous ones with Student's T test (or Wilcoxon) will be tested as factors associated with knowledge about LTBI. Variables tested in the bivariate analysis with p value < 0.20 will be taken to the multivariate analysis (logistic regression). In the end, it is expected to assume as factors associated with the lack of knowledge about LTBI those variables that, at the end of the multivariate analysis, present a value of p <0.05. Data will be collected through an electronic questionnaire with pre-coded and open questions, previously tested in a group of subjects similar to those included in the research to confirm the adequacy of the instrument, aiming at the quality of the information obtained.

Textual responses will be coded. The variables will be grouped as follows: adequate or sufficient and insufficient knowledge.

In the outcomes in relation to CAP, the variables will be grouped as follows: adequate or sufficient knowledge regarding the adequacy of the prescription in both doses and inadequate or insufficient knowledge, when knowing the adequacy of only one of the doses. The attitude will be considered adequate when it agrees with the indication of treatment for all the nominees and inappropriate when it does not agree or does not carry out the indication. Regarding the practice of indicating treatment, it will be divided into two groups: those that indicate treatment for LTBI (group 1) and those that do not (group 2).

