Similarly, professionals who participate in the dispensing process at baseline will be evaluated. The variables will be grouped as follows: adequate or sufficient knowledge, when the professional is able to identify the use of Isoniazid 100mg and use of Isonizaide 300mg and inadequate or insufficient, when knowing the indication for the use of only one of the doses. The attitude will be considered appropriate when in possession of the prescription, the professional checks the presentation of Isoniazid and inappropriate when not checking before dispensing the drug. Regarding the practice, it will be divided into two groups: those who keep the two presentations in different places (group 1) and those who keep the two presentations in the same place (group 2).

[figure not shown]

[figure not shown]

[figure not shown]

[figure not shown]

[figure not shown]

[figure not shown]

[figure not shown]

[figure not shown]

[figure not shown]

Figure 3- timeline for selecting the study sample

Third Stage

It will be a qualitative research that, according to Denzin and Lincoln (2006), involves an interpretive approach to the world, which means that its researchers study things in their natural settings, trying to understand phenomena in terms of the meanings that people give to them. The theoretical axis adopted will be that of social representations, understood as modalities of practical knowledge, oriented towards communication and understanding of the social, material and ideational context in which we live.

The contents expressed by the individual are essentially heterogeneous; they translate the thinking, the common sense of a given social group, understanding the individual in a social perspective, because reality is socially constructed (SPINK, 2004). For Marx (1994) the human essence is not something abstract and immanent to each individual. It is, a reality, built in the set of social relationships that can be reported, can be observed; the speeches and experiences of social actors provide relevant data for the researcher, through meetings and conversations, to expand access to the production of meaning and the representations of individuals constructed (SPINK, 2004).

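### The stage 2 prescriber practice and attitude scores do not measure compliance in prescribing Isoniazid 300mg, and the single June 2018 wave can describe only readiness at introduction

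*Protocol*

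**What the plan says.** The Objective section ties two aims to the knowledge, attitudes and practices method. One is "To analyze compliance in the prescription of Isoniazid 300mg for the treatment of latent tuberculosis infection through the Knowledge, Attitudes and Practices (CAP) strategy"; the other is the matching aim for dispensing. The Introduction also gives checking compliance in both activities as the purpose of stage 2.

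The stage 2 Data analysis section then defines the scores. Prescriber practice has two groups: "those that indicate treatment for LTBI (group 1) and those that do not (group 2". Prescriber attitude is adequate when the respondent agrees with the treatment indication. Prescriber knowledge is adequate when it covers prescribing in both doses. For dispensers, the text says that "professionals who participate in the dispensing process at baseline will be evaluated", and the three scores are knowing the use of each presentation, checking the presentation before dispensing, and storing the two apart.

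On who is surveyed, the first-step Methods text says "The health facilities that prescribe LTBI treatment will be chosen". The section on selecting facilities uses the number treated in the previous year. Stage 2 invites the staff of those same units who prescribe, dispense or monitor LTBI treatment.

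On timing, the Schedule lists "Conducting the Cross-sectional Study | June/2018" once, and for the trial "Period of insertion of participants | June/2018 to March/2019".

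**The concern.** The objective concerns how a particular presentation is prescribed. The two scores meant to capture what prescribers do and what they hold concern whether LTBI should be treated at all. The errors that the protocol itself fears are confusions between tablet strengths; the plasma subanalysis describes both underdosing and overdosing of that kind. A prescriber whose prescriptions invite such confusion would score as well on practice and attitude as one whose prescriptions do not.

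Two features add to this. Selecting units that already treat LTBI leaves the practice score little room to vary. A single wave in the first enrolment month can also record only limited experience with 300mg under the trial. At stake is a stage 2 report that speaks of compliance in prescribing 300mg on the strength of scores that never refer to it.

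**Working it through.** **1. Each score against the objectives (stage 2 Data analysis section).**

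| Score | What is recorded | Refers to the doses or presentations? |
| --- | --- | --- |
| Prescriber knowledge | adequacy of prescribing in both doses | yes |
| Prescriber attitude | agrees with the indication | no |
| Prescriber practice | indicates LTBI treatment or not | no |
| Dispenser knowledge | use of each presentation | yes |
| Dispenser attitude | checks the presentation before dispensing | yes |
| Dispenser practice | stores the two apart or together | yes |

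Four of the six scores bear on the doses or presentations. The two that do not are both on the prescriber side, and they are the two that come closest to behaviour.

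**2. The survey's size.** The protocol gives a 70% hit ratio, 80% power, a 5% significance level, 47 subjects, a design effect of 1.2 and a final 56. It states no null value; 50% is assumed here. For a two-sided one-sample test of a proportion:

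n = [1.96·√(0.5·0.5) + 0.84·√(0.7·0.3)]² / (0.7 − 0.5)² = 46.63, rounded up to 47.

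Then 47 × 1.2 = 56.4, stated as 56. The figure reproduces and is not in dispute. It is sized for one proportion at one time.

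**3. How little the practice score may vary.** The protocol gives no share of staff who indicate treatment, so a range is assumed. The expected number in the second group is 56 × (1 − share):

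- 80%: 56 × 0.20 = 11.2
- 90%: 56 × 0.10 = 5.6
- 95%: 56 × 0.05 = 2.8
- 98%: 56 × 0.02 = 1.1

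These counts suppose that all 56 respondents answer the item. Only prescribers would, so the real counts would be smaller.

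**4. Experience with 300mg by the end of June 2018.** The centre targets are 186 + 4 × 90 = 546. Enrolment runs for 10 months. Even accrual and equal arms are assumed.

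- All centres: 546 / 10 / 2 = 27.3 starts on 300mg per month
- A 90-person centre: 90 / 10 / 2 = 4.5 per month, spread over its units
- After 7 to 10 months in such a centre: 4.5 × 7 = 31.5 to 4.5 × 10 = 45

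These are trial starts only. Any 300mg prescribed outside the trial would add to them, and the protocol gives no figure for that.

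**The case against.** A reader might infer that stage 2 cannot answer either objective. The protocol does not support that. All three dispenser scores concern the two presentations, so the dispensing objective is addressed, although by self-report and early. Prescriber knowledge covers both doses, so part of the prescribing objective is addressed too.

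A reader might also infer that June 2018 is the first month in which 300mg is used. The Introduction says only that "from 2018, Isoniazid 300mg will also be made available to the health network", with no month. The first-step Methods text does label baseline as the period before 300mg is introduced, and stage 2 uses that word for dispensers. This makes the inference plausible, but it is not stated, and the word is not applied to prescribers.

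Nor is the objective on information strategies lost. It is not tied to the survey method, and the stage 3 interview guide asks directly whether the material on 300mg was sufficient.

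Three further objections are fair.

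- Units are selected but professionals are scored, so a treating unit may include staff who do not indicate treatment. Low variation is therefore likely, not guaranteed.
- The Introduction says that the trial itself will evaluate prescription and dispensing. However, its stated outcomes are treatment success and adverse effects, and its interviews cover intake and adverse effects. The plasma subanalysis does list dispensing below the prescribed strength, but in 36 people in the Federal District.
- The questionnaire appendix is not shown and may contain items specific to 300mg. The scoring rules are in the body of the protocol, though, and as written they would not use such items for prescriber practice or attitude.

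A survey at introduction is a recognised way to assess readiness, so the June date is not an error in itself.

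**Conclusion.** The point holds in a limited form. Prescriber practice and attitude, as defined, do not measure compliance in prescribing Isoniazid 300mg, although the protocol assigns that objective to stage 2. This follows from the text alone and needs no assumption.

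The practice score is also likely to be close to constant: about 11 to 1 of 56 in the second group for assumed shares of 80% to 98%, and fewer once only prescribers are counted.

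The single June 2018 wave reflects about 27 trial starts on 300mg across all centres by the end of that month, under even accrual and equal arms. It can support a description of readiness at introduction, but not of established practice. The dispensing objective is answered weakly and early; it is not left unanswered. The randomised comparison and the survey's sample size are unaffected.

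**What to change.** **Scores.** In the stage 2 Data analysis section, replace or supplement prescriber practice and attitude with presentation-specific scores. Examples are whether the prescriber states tablet strength and number of tablets, and whether the prescriber checks which presentation is being prescribed.

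**Records.** Where feasible, tabulate presentation prescribed against presentation dispensed, using records that the trial already generates. Comparison with the allocated presentation would instead measure adherence to randomisation.

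**Timing.** State that the June 2018 wave falls in the first month of enrolment and describes readiness at introduction, and limit the conclusions on compliance accordingly.

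**Cost.** The scoring rules and a few questionnaire items change, and records are checked where that is feasible. The trial's randomisation and outcomes do not change.

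**Optional repeat wave.** A second round late in enrolment would show practice after more use, but it has a price. The Data collect section places the survey at all five centres before the qualitative study, and the survey's final product is due in October 2018; both would have to be revised. The 56 subjects were not sized to detect change. An uncontrolled before-after difference should not be attributed to the information strategies.

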**SELECTION OF INDIVIDUALS AND RANDOMIZATION**

All individuals over 18 years of age with an indication for LTBI treatment between June 01, 2018 and March 30, 2019 at one of the centers selected for the study will be eligible. Individuals whose index case is retreatment, multidrug-resistant and extremely resistant will be excluded, as well as those individuals who were transferred from the original center after two or more weeks of starting treatment in addition to individuals from the prison system.

186 subjects will be included in Espírito Santo and 90 in each of the centers of the

study.

Study subjects will be randomized through a random number worksheet that will contain the treatment regimen in two study groups: Intervention Group: Isonizazide in the 300mg formulation and Control Group: Isonizazide in the 100mg formulation. Randomization will be by block. A randomization list with a random sequence of blocks of participants will be generated for each study center. This strategy ensures that the intervention group and the control group are balanced in terms of the number of participants. To ensure allocation confidentiality, sealed envelopes with the randomization sequence generated using the R software will be sent to each center during the study.

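### The schedule closes follow-up in November 2019, 216 to 245 days after the last permitted entry, too early for late entrants to complete the 270-dose, 9-to-12-month primary outcome

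*Protocol*

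**What the plan says.** Four statements in the Protocol bear on this.

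- **Entry** (SELECTION OF INDIVIDUALS AND RANDOMIZATION): adults are eligible "with an indication for LTBI treatment between June 01, 2018 and March 30, 2019". The SCHEDULE and the First step of METHODS agree on June 2018 to March 2019.
- **Primary outcome** (METHODS, First step): "the proportion of subjects with 270 doses of isoniazid between 9 to 12 months". The INTRODUCTION describes the same course, "in 270 doses that should be taken from 9 to 12 months", of a drug given "in a dosage of 5 to 10 mg/kg/day".
- **Duration of follow-up** (METHODS, First step): randomised contacts "will be followed up until the end of treatment". Phase 2- Follow-up places the last interview at that same point.
- **Close of follow-up** (SCHEDULE): "Closing of follow-up of patients included in the Pragmatic Trial | November / 2019". No day is given. Analysis and delivery of the trial results are both set for December 2022.

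Nothing in the Protocol extends follow-up past November 2019 or says how a participant still on treatment at that date is classified.

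**The concern.** The entry period, the outcome window and the closing date are all fixed, and they cannot all hold for people who enter late. Someone randomised at the end of March 2019 who takes every dose on time is still on treatment when the schedule stops collecting outcomes. For that person the primary outcome is unobserved because of the calendar, not because of adherence.

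Depending on how such people are handled, the reported success rate may be understated in both arms, calendar truncation may be mixed with abandonment, or the sample may shrink. The Protocol also gives its centres two different stopping points for the same outcome, so centres may act differently.

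**Working it through.** **Dates for the last entrant (30 March 2019), one dose per day**

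- Dose 270, starting on the day of entry: 30 March 2019 + 269 days = 24 December 2019.
- End of 9 months: 30 December 2019. End of 12 months: 30 March 2020.
- Time to closure: 216 days to 1 November 2019, 245 days to 30 November 2019. Both are below 270, so even the most favourable day in November fails.

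**Share of participants affected.** The Protocol gives no accrual curve, so I assume uniform entry over the 302 days from 1 June 2018 to 30 March 2019. If completion needs T days and the last entrant has L days, the share who cannot finish is (T − L)/302.

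| | Close 30 Nov (L = 245) | Close 1 Nov (L = 216) |
|---|---|---|
| Cannot reach 270 doses (T = 270) | 25/302 = 8.3% (45 of 546) | 54/302 = 17.9% (98 of 546) |
| Lack the full 12 months (T = 365) | 120/302 = 39.7% | 149/302 = 49.3% |

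Counting the entry day as the first dose day gives 24/303 = 7.9% and 53/303 = 17.5%. The second row includes the first: those in it who can reach day 270 can still succeed, but with a shortened allowance.

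**Baseline power.** SAMPLE SIZE CALCULATION assumes abandonment of 30% vs 19%, that is, success of 70% vs 81%. The stated 474 reproduces as a total: 237 per arm gives 80% power at two-sided 5%. The inflated 546 equals the centre targets (186 + 4 × 90), hence 273 per arm. I use

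power = Φ{[|p1 − p2|√n − 1.96√(2p̄(1 − p̄))] / √[p1(1 − p1) + p2(1 − p2)]}.

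With n = 273, 0.70 and 0.81: (0.11 × 16.52 − 1.96 × 0.608)/0.603 = 1.04, so power is 85%. This treats all 546 as observed; the Protocol plans 80% after losses.

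**Power under truncation.** Let u be the share of would-be completers cut off. For completion spread evenly over a range of days, u is (mean T − L)/302. The range of completion times is my assumption.

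| Completion time | Close | u | Scored as non-success: rates | Power | Excluded: n per arm | Power |
|---|---|---|---|---|---|---|
| Exactly day 270 | 30 Nov | 8.3% | 64% vs 74% | 72% | 250 | 82% |
| | 1 Nov | 17.9% | 57% vs 67% | 59% | 224 | 77% |
| Days 270–300 (mean 285) | 30 Nov | 13.2% | 61% vs 70% | 65% | 237 | 80% |
| | 1 Nov | 22.8% | 54% vs 62% | 52% | 211 | 75% |
| Days 270–365 (mean 317.5) | 30 Nov | 24.0% | 53% vs 62% | 51% | 207 | 74% |
| | 1 Nov | 33.6% | 46% vs 54% | 40% | 181 | 68% |

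The non-success columns multiply 70% and 81% by (1 − u). The exclusion columns keep 70% vs 81% and multiply 273 by (1 − u), removing the same share from both arms.

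**If the outcome is abandonment before closure**, and those still on treatment are not counted as abandoning, little is lost. With abandonment spread evenly over days 0 to 270 (again my assumption), the rates are 29.9% vs 18.9% or 29.5% vs 18.7%, and power is 84% to 85%.

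**Loss allowance.** The 15% allowance is 546 − 474 = 72 participants. If those who cannot reach day 270 count as lost, 45 to 98 are used, from well over half of the allowance to more than all of it.

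**Relative risk.** Truncation common to both arms leaves the relative risk of success at 0.81/0.70 = 1.16. If the truncated are scored as non-success, the relative risk of non-success moves from 0.19/0.30 = 0.63 towards 1, to between 0.72 and 0.86. That is dilution and favours neither arm.

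**The case against.** The strongest reply is that the SCHEDULE entry is a planning line at month level, and that the operative rule is the one in METHODS: follow each participant to the end of treatment. Follow-up is also entered in the local notification systems for LTBI treatment, so outcomes may be retrievable whatever the closing date. This may well be what centres do. It does not remove the conflict, because the Protocol does not say which statement prevails or that those systems supply the outcome after closure.

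Three stronger readings are tempting, and the document does not support them.

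- *Power collapses to about 40%.* That needs uniform accrual, scoring of all truncated participants as non-success, completion spread up to day 365 and closure on 1 November. The Protocol states none of these. The intention-to-treat population in ANALYSIS PLAN keeps everyone in regardless of loss to follow-up, which makes such scoring plausible but does not prescribe it.
- *Up to half of the participants are denied the outcome.* The 40–49% lack the full allowance, but 12 months is an upper limit for taking 270 doses, not a required duration. Only about 8–18% cannot reach it.
- *The comparison is biased towards one arm.* Randomisation is in blocks within each centre, so entry dates, and with them truncation, should be about equal between arms.

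The plasma subanalysis labels the sixth month as the end of treatment, and a reader might infer that November 2019 is late enough. The primary outcome is nevertheless fixed at 270 doses within 9 to 12 months, so that label does not help here.

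**Conclusion.** The contradiction stands on the Protocol's own dates and needs no outside figure. November 2019 is too early for the last entrants under any reading of the day, and it conflicts with following participants to the end of treatment.

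The consequence is less certain than the dates. The 8–18% rests on uniform accrual. Power at 273 per arm ranges from about 40% to close to the undiluted 85%, mainly according to a classification rule that the Protocol does not give. What is at risk is the absolute success rate and the precision of the comparison; the relative risk of success is not pushed towards either arm. Because the primary outcome is affected and data not collected cannot be recovered by analysis, the dates should be corrected.

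**What to change.** Reconcile the SCHEDULE with METHODS and with SELECTION OF INDIVIDUALS AND RANDOMIZATION by moving the close of follow-up to 30 March 2020, 12 months after the last permitted entry. Every participant then has the whole outcome window, and the classification of people still on treatment at closure no longer matters within that window.

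The cost is four more months of outcome collection from 30 November 2019, or nearly five from 1 November. METHODS already implies this work, and analysis can stay in December 2022. The BUDGET does not state the period it covers, so funding for the extra months needs checking.

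Keeping November 2019 and ending enrolment 12 months earlier would also remove the conflict, but it would cut recruitment from ten months to five or six. I do not recommend it.
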